## Abstract

**Introduction:**

Genitourinary Syndrome of Menopause (GSM) defines a set of symptoms associated with an estrogen deficit involving alterations in organs genitourinary and that results in several urinary, genital, and sexual alterations. Brazilian women live about a third of their life after menopause, where hormonal changes occur along with clinical manifestations, characterized by vaginal and vulvar dryness, burning sensation, discomfort, vulvovaginal irritation, lack of lubrication, dyspareunia and urinary incontinence. Fractionated photothermolysis and radiofrequency systems, alone or in combination were tested to improve GSM.

**Objective:**

The goal of this study is to elaborate a protocol to evaluate the clinical response of patients with symptoms of GSM after the application of photobiomodulation in the vulvar region.

**Method:**

In this randomized, double-blind, placebo-controlled study protocol, women over 50 years of age who are in the postmenopausal period (amenorrhea for at least 12 months, with no pathology involved) with one or more symptoms of GSM will be randomly divided into two groups. The treatment group (n = 30) will receive four consecutive applications, weekly, using DMC laser diode (λ = 808 nm), 4J per point, 100mW of power, 1,016W/cm^2^, 8 sites in the vulvar region, The Placebo Group (n = 30) will be handled as treated, but with the laser turned off. The quality of life will be assessed using female sexual functioning index (FSFI-6), urinary incontinence questionnaire (ICIQ-SF), Quality of life will be analyzed using the female sexual functioning index (FSFI-6). The intensity of menopausal symptoms will be evaluated using a visual analogue scale (VAS), the vulvo vaginal atrophy will be measured by the Vaginal Health Index (VHI). Also, the vaginal temperature will be measured using a thermal camera, the pressure of the pelvic floor force (vaginal dynamometer) and a 1-hour Pad Test will be performed to quantify the urinary loss. With this procedure, we intend to obtain an overall better life quality and diminished symptoms in women with GSM. All assessments will be performed prior to the first irradiation and after the last one.

**Trial registration:**

This protocol is registered at ClinicalTrials.gov under the number NCT05557799.

## Introduction

### Study design

This study protocol was designed as a prospective, randomized, double-blind, controlled trial according to the 2023 SPIRIT (Standard Protocol Items: Recommendations for Interventional Trials) Statement and SPIRIT (Fig 3) and it will be conducted at Nove de Julho University and the Municipal Health Department of Vargem Grande Paulista, SP in 2023–2024. Fig 1 shows the SPIRIT statement. All participants were required to sign an informed written consent. The recruitment will be held from February 01^st^ 2024 to June 30^rd^ 2024

**Fig 1 pone.0313324.g001:**
[figure not shown]
Cellular mechanisms of PBM.

### Contextualization

Genitourinary Syndrome of Menopause (GSM) refers to a set of symptoms and signs associated with estrogen deficiency, characterized by changes in the genitourinary organs resulting in various urinary, genital, and sexual alterations [1].

GSM or its characteristics manifest in approximately 15% of women in the premenopausal stage and 40–54% of women in the postmenopausal stage [2, 3]. In the United States, GSM is estimated to affect 8% to 22% of women in the premenopausal stage and 40% to 57% of women in the postmenopausal stage. Surprisingly, only 1 in 5 women experiencing GSM-related symptoms seek medical attention [4]. International literature indicates that only 59% of these women seek medical help, whereas in Europe, only 4% of women report vulvovaginal symptoms. About 25% of women with GSM seek medical care, and only 54% discuss their sexual health with healthcare professionals when asked, while 33% choose not to address this issue during a consultation [5].

In Brazil, studies show that only 59% of women experiencing symptoms related to urogenital atrophy seek medical help. The complaint of vaginal dryness is present in 34.9% of women, and respondents reported that the climacteric negatively impacts their sexuality. In the United States, 59% of women reported sexual dissatisfaction [6–8].

Among the observed signs and symptoms, studies found a high frequency of complaints such as dyspareunia (44%), irritation (37%), vaginal dryness (55%), recurrent urinary tract infections (5% to 17%), and urge incontinence in women above 60 years (15% to 35%). The prevalence of atrophic vaginitis was 4%, increasing to 25% in the first year after menopause and 47% after three years. Note that dyspareunia leads to a reduction in the frequency of sexual intercourse, with 72% of women having intercourse only once a month and 34% weekly [9, 10].

The complaint of chronic incontinence is one of the main signs and symptoms of genitourinary syndrome in postmenopausal women. Studies point out that the loss of conscious and voluntary bladder control is a common problem that can affect anyone, but its prevalence increases in the female sex and with advancing age [11]. With the increase in women’s life expectancy, urinary incontinence must be considered a concern by healthcare professionals, directly affecting healthy aging and quality of life in this age group. About 10% of women visiting the gynecologist list urine loss as their main complaint, which represents a negative impact on quality of life [12–14].

This condition is often treated with physiotherapy, which aims to educate about urinary function, utilize pelvic floor muscle (PFM) function, and strengthen these muscles through techniques and exercises [15]. Common interventions in physiotherapy include kinesiotherapy (with or without vaginal cones), electrostimulation, biofeedback, behavioral therapy, and body awareness within primary and secondary healthcare services [16].

Vaginitis is also a common complaint in GSM, and gynecologists usually recommend hormonal and non-hormonal treatments to address it. Non-hormonal lubricants and moisturizers can be helpful for mild to moderate vaginal dryness, but they might interfere with sexual spontaneity and be impractical in application, leading to low long-term adherence. On the other hand, topical estrogen application is considered the "gold standard" treatment for moderate to severe cases or those not responsive to non-hormonal treatments [17].

However, topical estrogen application has limitations, such as: lack of long-lasting action, high recurrence rate after discontinuation, and action limited to the vaginal epithelial surface without effects on extracellular matrix renewal and vascularization. Additionally, many women discontinue treatment due to the risk of developing hormone-dependent neoplasms in the long term [18, 19].

Alternatively, various types of treatments using a photothermal approach with CO2 lasers, fractional lasers, Er:YAG lasers, and radiofrequency systems, either individually or in combined therapy, have shown improvement in GSM symptoms, promoting morphological changes in vaginal tissues and increasing vaginal blood circulation. Patients report improvement in vaginal dryness, dyspareunia, and stress urinary incontinence [20]. However, the high cost of this method as well as its side effects such as pain and erythema may limit its use in public healthcare [21].

Alternatively, photobiomodulation therapy (PBM) is a different approach that is practical, safe, painless, well-tolerated, without immediate or delayed complications, and can be applied on an outpatient basis for the treatment of GSM. This is particularly relevant for women with atrophic vaginitis (AV) and a history of hormone-dependent neoplasia, for whom estrogen therapy is contraindicated [22].

Photobiomodulation therapy utilizes light at appropriate radiometric parameters that triggers a cascade of cellular effects that result in alterations in local tissues. The primary mechanism proposed to explain the effects of red and infrared light involves modifications in mitochondrial activity, especially in the enzyme cytochrome C oxidase (COX), present in damaged or hypoxic cells [23].

The biochemical mechanism underlying the therapeutic effects PBM is not fully elucidated, nevertheless there is robust evidence indicating that it acts on mitochondria to stimulate adenosine triphosphate production, modulate reactive oxygen species (ROS), and induce transcription factors. Several of these transcription factors are regulated by changes in cellular redox state. These include redox factor-1 (Ref-1), activator protein-1 (AP-1) (a c-Fos and c-Jun complex), nuclear factor kappa B (NF-κB), p53, cyclic AMP response element-binding protein (ATF/CREB), hypoxia-inducible factor (HIF)-1, and HIF-like factor [24, 25]. These transcription factors then trigger protein synthesis, resulting in subsequent effects such as increased cell proliferation and migration, modulation of cytokine levels, growth factors, inflammatory mediators, and enhancement of tissue oxygenation [26].

Fig 2 illustrates the mechanism of action of PBM at the cellular and molecular levels.

**Fig 2 pone.0313324.g002:**
[figure not shown]
SPIRIT figure for the schedule of enrolment as recommended by 2013 SPIRIT statement.

Immune cells, such as mast cells, are strongly influenced by PBM, where specific wavelengths of light are capable of triggering mast cell degranulation. PBM also enhances the proliferation, maturation, and motility of fibroblasts, leading to increased production of basic fibroblast growth factor, thereby promoting faster tissue healing [27]. In addition, it can induce vasodilation by triggering relaxation of smooth muscle associated with the endothelium, which is highly relevant for inflammation treatment. This vasodilation enhances oxygen availability to treated cells and allows for increased immune cell trafficking into tissues. These two effects contribute to accelerated healing [28].

Given the current advancements and limitations in the field, there is a significant need for innovative therapeutic strategies to manage Genitourinary Syndrome of Menopause (GSM) in women experiencing urinary incontinence. Therefore, the objective of this study is to evaluate the effects of photobiomodulation on clinical outcomes in postmenopausal women presenting with GSM and urinary incontinence, utilizing a randomized, placebo-controlled clinical trial design.

To our knowledge, this study is the first protocol to investigate photobiomodulation therapy in patients with Genitourinary Syndrome of Menopause.

## Methods

### Ethics

This study is a placebo-controlled, randomized, and double-blind clinical protocol, approved by the Research Ethics Committee of Nove de Julho University (Uninove) number 5.628.333 and approved by the Municipal Health Department of Vargem Grande Paulista, SP.

### Sample size and participants

Since the literature lacks studies on the effects of the photobiomodulaton on GSM, the sample size was calculated using the formula described using the estimated effect size, as described by Kadam and Bhalerao [29]. Considering a type I error of 0.05 and a test power of 80%, the calculated sample size was 60 participants, with 30 in each group (A and B). The Fig 3 shows that, for medium (0.750) and large effects (1.000–1.250), a minimum of 30 patients per group is sufficient to control statistical variance, ensuring a test power greater than 0.80. Considering a 10% of sample loss, a total of 66 patients will be recruited for the study. The Fig 3 shows a plot of the test power as a function of the sample size and estimated effect size.

**Fig 3 pone.0313324.g003:**
[figure not shown]
Test power analysis as a function of effect size and sample size.

#### Recruitment

Recruitment will be conducted through the public health system of Vargem Grande Paulista, SP, Brazil. Additionally, recruitment efforts were carried out through the municipality’s Senior Center, social media, and referrals from participants who had previously undergone the project.

### Inclusion and exclusion criteria

#### Inclusion

Women over 50 years old in the postmenopausal period (amenorrhea for at least 12 months without involved pathology);Presenting one or more symptoms of GSM (such as dyspareunia, dryness, irritation, vaginal burning and/or discomfort, vaginal and vulvar atrophy, vaginal dryness, dysuria, polyuria, recurrent urinary infections);With complaints of stress and/or urgency urinary incontinence;Presenting a normal cervical cytology (Pap smear) performed within the last year.

#### Exclusion

Woman on hormonal medication for menopausal symptoms in the last 6 months;Participants who explicitly declined to participate;Participants who had a history of bilateral oophorectomy;Subjects with conditions such as:
○ recent Acute Myocardial Infarction (AMI);○ neoplasms;○ history of thrombosis;○ liver insufficiency;○ uncontrolled genital bleeding;○ genital condylomatosis;○ active genital herpes.Subjects with surgeries of the lower genital tract that would preclude treatment;Subjects with photosensitivity.

### Strategies to improve adherence of the participants to the protocol

The participants will be included in a phone message group through which they will be reminded of the follow-up appointments by the researchers.

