### Blinding

Both the person evaluating the VHI and the participants will not be informed about the group assignments. This ensures that neither the evaluator nor the participants know which group the participants are in (blinding).

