#### Photobiomodulation protocol

The photobiomodulation cohort was subjected to the prescribed irradiation regimen in the subsequent manner. Each participating individual will undergo a standardized treatment protocol, involving a one irradiation session per week administered over a span of four consecutive weeks. During each individual session 4 J of radiant energy per application site will be imparted. This energy will be emitted at a wavelength of 808 nm and was delivered through employment of a DMC laser system, specifically the Therapy XT model (Fig 5). The laser system exhibited a radiant power output of 100 mW, and the duration of irradiation for each distinct application site was precisely maintained at 40 s. The laser will be hovering close to the surface of the vaginal region. The detailed radiometric parameters can be observed in Table 1.

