**Fig 6 pone.0313324.g006:**
[figure not shown]
Anatomic sites irradiated.

The sham group underwent the same protocol, but the laser was turned off during the whole procedure.

At the end of the fourth session all subjects underwent a final pelvic pressure and urinary loss assessment.

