## Study limitations

The main limitation of this study is the short evaluation period of 90 days, which may be insufficient to determine the long-term efficacy and durability of photobiomodulation therapy for treating GSM symptoms. Additionally, the reliance on self-reported data could potentially introduce bias due to subjective interpretations and reporting inaccuracies by participants.

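### The shared phone message group opens a channel between participants that non-disclosure cannot close, a risk to the participant blind for the self-reported outcomes

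*Protocol article*

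**What the plan says.** Four places in the protocol article bear on this point.

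- **Strategies to improve adherence:** "The participants will be included in a phone message group through which they will be reminded of the follow-up appointments by the researchers". Arms are not mentioned. Nor is it stated whether members can see or answer one another.
- **Blinding:** "Both the person evaluating the VHI and the participants will not be informed about the group assignments". The next sentence draws the conclusion: "This ensures that neither the evaluator nor the participants know which group the participants are in (blinding".
- **Photobiomodulation protocol, end of section:** "The sham group underwent the same protocol, but the laser was turned off during the whole procedure". No masking of light, sound or indicator is described.
- **Study limitations:** the authors accept that "the reliance on self-reported data could potentially introduce bias due to subjective interpretations and reporting inaccuracies by participants".

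Under Outcomes, the FSFI, the ICIQ-SF and the VAS for each symptom are completed from the participant's own report. The VHI, vulvar temperature, pelvic pressure and pad weight are not.

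**The concern.** The participant blind rests on staff not disclosing the assignment. That controls what staff tell participants, but not what participants learn from each other. A message group, in the ordinary sense of the word, is a place where members can talk. Read plainly, the adherence section puts all participants in one such group. Splitting it by arm would not help, because membership would then mark allocation.

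The blind is the main protection for the self-reported outcomes. If women come to believe, correctly more often than chance, that they had the active or the switched-off laser, their ratings can shift apart between arms without any effect of treatment. The analysis cannot separate such a shift from a real difference.

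**Working it through.** **1. The passages side by side.** The Blinding section has one mechanism, non-disclosure, and claims that it *ensures* ignorance of the assignment. The adherence section sets up a channel linking participants and states no restriction on it. The two do not contradict each other, but the guarantee is stronger than the mechanism behind it.

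**2. What must hold for the channel to do harm.**

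- (a) Members can see and write to each other. The article is silent.
- (b) What they exchange carries information on allocation. There are two possible sources:
  - *Session experience.* This is informative only if active and switched-off sessions differ perceptibly. The article gives the emission ("This energy will be emitted at a wavelength of 808 nm", 100 mW, 40 s per site) but does not say what a participant can see, hear or feel.
  - *Symptom change.* This needs no device difference, but it points to allocation only if the treatment works. With no true effect, symptom change says nothing about the arm.
- (c) The belief alters what is reported. This can apply to FSFI, ICIQ-SF and VAS.

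It follows that false-positive inflation under no true effect depends on a perceptible session difference. Guesses unrelated to the true arm do not produce a systematic difference between arms.

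**3. The plan's own figure.** The Sample size section ("Considering a type I error of 0.05 and a test power of 80"%) gives 30 per group and names a standardised effect of 0.75 as medium.

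- Normal approximation: n = 2 × (1.960 + 0.842)² / 0.75² = 27.9, so 28 per arm.
- Two-sample t-test: 28.9, so 29 per arm.
- Power at 30 per arm: 0.828 (normal) or 0.815 (t).
- Allowance for loss: 60 × 1.10 = 66.

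The stated 30 per arm is reproduced within 2, so it is a sound base for the illustration.

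**4. Illustration of a pure bias.** Assume no true effect and a between-arm shift of b SD in a self-reported outcome. The two-sided t-test at 0.05, as in Statistical analysis, then rejects with the power it would have against a real effect of size b. With n = 30 per arm, the degrees of freedom are 58, the critical value is 2.002, and the noncentrality is b × √(30/2) = 3.873 × b.

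| Assumed shift b (SD) | Noncentrality | Probability of p < 0.05 |
|---|---|---|
| 0 | 0 | 5.0% |
| 0.1 | 0.387 | 6.7% |
| 0.25 | 0.968 | 15.9% |
| 0.5 | 1.936 | 47.8% |

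The shifts are assumptions. Nothing in the article gives a size for them or links a reminder group to any particular value.

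**The case against.** The strongest reply is that the text describes only messages from researchers to participants. The channel may already be one-way, and a journal article may leave such settings to the full protocol. This stands as a reason not to assert that women of both arms are in open contact. It does not remove the point: the article chose the word group, fixed it as a procedure, and claimed that the blind is ensured. One clarifying phrase would settle it.

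A reader might also infer several stronger things that the documents do not support:

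- **That the blind is broken because a switched-off laser is easy to recognise.** No passage says the sessions look, sound or feel different, so comparing notes need not reveal allocation.
- **That recruitment through "referrals from participants who had previously undergone the project" is a second route to unblinding.** The text does not say that these women were randomised in this trial. If they were, they too were not told their assignment. Any expectation they pass on arises before randomisation and so falls on both arms.
- **That most outcomes are exposed.** By instrument, three are self-reported (FSFI, ICIQ-SF, VAS) and four are not (VHI, vulvar temperature, pelvic pressure, pad weight). Urinary loss, central to the hypothesis, is also weighed.
- **That 16% or 48% is the trial's error rate.** Any bias of the same size from any source gives the same figures, and at 0.1 SD the rate is only about 7%.
- **That the group breaches privacy.** This turns on member visibility and on what participants agreed to, neither of which the available text shows.

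**Conclusion.** The point holds as a credible, avoidable risk to the participant blind. It is neither a demonstrated break nor a contradiction in the text. What the article does establish is narrow: participants are placed in a message group with no stated limit on contact, and the Blinding section claims more than non-disclosure can deliver.

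The consequence is confined to the FSFI, ICIQ-SF and VAS comparisons. It rests on two things the article leaves open: that members can communicate, and that what they share is informative about allocation. The size is unknown. The illustrative range of about 7% to 48% for assumed shifts of 0.1 to 0.5 SD shows only that a trial of 30 per arm has little tolerance for a moderate reporting bias. Since removing the channel costs almost nothing, the change is worth making.

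**What to change.** 1. In the adherence section, replace the message group with individual messages, or with a one-way broadcast in which recipients can neither see nor reply to each other. If this is already the practice, say so. A group already running can be switched to this setting.
2. Ask participants at enrolment not to discuss their sessions with other participants until the trial ends.
3. In the Blinding section, replace the claim that non-disclosure ensures the blind with a statement of the measures taken, including whether the switched-off device can be told from the active one.

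A question on guessed allocation at the final assessment is optional. Reminders are kept in full, and treatment, sample size and analysis are unchanged. The only cost is slightly more messaging work.

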### Randomization

The participants were randomly assigned to two groups, Group A (treatment) and Group B (placebo), in block-randomization fashion, with each block comprising four participants. After participant selection and assessment, sealed brown envelopes were randomly assigned to each subject containing the treatment allocation until the block was over, afterwards a new block of four allocation (two in each group) was made.

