### Statistical analysis

The data will be tested for normality using the Shapiro-Wilk test, and those with parametric distribution will be represented by their respective means and standard deviations. In cases where the assumption of parametric distribution is rejected, medians and quartiles will be used. To assess the association between the studied groups and the independent variables, Student’s t-test or Wilcoxon-Mann-Whitney test will be used for parametric and non-parametric data, respectively. All tests will be two-tailed, and the adopted significance level is α = 0.05. The results will be organized in excel spreadsheet and the inferential analysis will be conducted using R.

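### A single block size of four, filled one block at a time, lets anyone who knows past allocations deduce about a third of all allocations with certainty

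*Protocol article*

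**What the plan says.** The Randomization section of the protocol article assigns women to treatment or placebo "in block-randomization fashion, with each block comprising four participants". It names no strata. On the mechanism it says that "sealed brown envelopes were randomly assigned to each subject containing the treatment allocation until the block was over", and then that "afterwards a new block of four allocation (two in each group) was made". Assignment follows selection and assessment. The Research flow text under Interventions likewise puts the gynecological examination, the eligibility check and the baseline pelvic pressure and urinary loss measurements before assignment.

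On who knows the arm, the Blinding section says: "Both the person evaluating the VHI and the participants will not be informed about the group assignments". It lists nobody else. The Photobiomodulation protocol section describes the control: "The sham group underwent the same protocol, but the laser was turned off during the whole procedure". The Sample size section plans 30 women per group and recruits 66 to allow for losses.

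**The concern.** Every block holds two of each arm in four places, and there is one sequence for the whole trial. Anyone who can count allocations therefore knows where a block starts and ends. Whoever runs the sessions knows whether the laser was on. Sealing the envelopes does not help, because the deduction comes from earlier allocations and the block size, not from looking inside an envelope.

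What is at stake is allocation concealment. If someone who can foresee the next arm also influences which woman is approached, or when she enters, the arms can differ in prognosis. The Statistical analysis section plans a t-test or a Wilcoxon-Mann-Whitney test between groups and describes no baseline adjustment, so such a difference would pass into the result.

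**Working it through.** **Inputs.** Block size 4 and a 2:2 split (Randomization). Target of 30 per group, 66 recruited (Sample size and participants). "All tests will be two-tailed", at 0.05 (Statistical analysis). The article gives no figure for predictability, so there is none to reproduce. Its sample size is consistent with its inputs: for a standardized effect of 0.75, power at 30 per group is 0.815 by noncentral t, above the stated 0.80.

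**Certain deductions.** A 2:2 block has C(4,2) = 6 equally likely sequences. A place is certain once both places of one arm are used.

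- Places 1 and 2: never certain.
- Place 3: certain when the first two agree, in 2 of 6 sequences, so 1/3.
- Place 4: always certain.

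Per full block: (0 + 0 + 1/3 + 1)/4 = 33.3%. For 66 women there are 16 full blocks plus two places: 16 × 4/3 = 21.3, and 21.3/66 = 32.3%.

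**Best guess.** Guessing the arm that is behind is right with probability 1/2, 2/3, 2/3 and 1 at places 1 to 4. The mean is 2.833/4 = 70.8% per full block. Over 66 women it is (16 × 2.833 + 1/2 + 2/3)/66 = 70.5%, against 50% with no information.

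**Conditional effect on type I error.** Assume that every deducible place is exploited, and that women entered at places known to be active differ in prognosis by s SD from those entered at places known to be sham. One third of each arm is affected, so the bias is s/3. With 30 per arm the noncentrality is (s/3) × √15, with 58 degrees of freedom. The extra spread that selection adds within arms is ignored. The values of s are assumptions, because the article gives none.

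| Assumed s (SD) | Bias (SD) | Type I error |
|---|---|---|
| 0.1 | 0.033 | 5.2% |
| 0.25 | 0.083 | 6.2% |
| 0.5 | 0.167 | 9.7% |
| 0.75 | 0.25 | 15.9% |
| 1.0 | 0.333 | 24.6% |

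**Alternatives.** These were simulated over 66 women against an observer who knows all past allocations and the set of possible sizes, each size being equally likely.

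| Block sizes | Certain | Best guess right |
|---|---|---|
| Fixed 4 | 32% | 70% |
| Mixed 2, 4, 6 | 4% | 70% |
| Mixed 4, 6 | 5.5% | 69% |
| Mixed 4, 6, 8 | 2% | 68% |

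A larger fixed size helps much less: by enumeration, 25% of places are certain with fixed blocks of 6 and 20% with fixed blocks of 8.

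**The case against.** The strongest objection is that predictability harms a trial only if someone who decides whom or when to enrol also knows past allocations, and the article does not say that. It supports such knowledge for the person operating the laser. It does not say that this person recruits, screens or holds envelopes, or that site staff were told the block size. This stands, and it makes any selection bias conditional.

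The existing safeguards also count. Assignment comes after assessment, and neither the VHI evaluator nor the participants are told the arm. This limits tampering with eligibility or baseline records. It does not stop a person who foresees the next arm from influencing who comes next, and recruitment through a senior center, social media and referrals leaves some discretion over order of entry.

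Three stronger readings are tempting, but the document does not support them.

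- A reader might infer that the envelopes leave no audit trail. The article does not say whether they were numbered or logged, and an article commonly leaves that to the full protocol. Drawing envelopes at random within a block is also a valid permutation and adds no predictability.
- A reader might take 9.7% as the type I error. It is one point on an assumed range, with full exploitation.
- A reader might conclude that no analysis could repair the damage. Adjustment for measured baseline values could remove part of such an imbalance, though not what was unmeasured.

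**Conclusion.** The point holds in conditional form. The stated scheme makes 33% of allocations in full blocks, about 21 of 66, certain to anyone who knows the past allocations and the block size. That figure is exact arithmetic on a stated rule. The sham procedure gives the knowledge of past allocations to whoever delivers the sessions. The step from there to selection bias is not documented, so its size is unknown. The range of 5.2% to 24.6% rests on an assumed difference of 0.1 to 1.0 SD with every deducible place used. This is a weakness of a design choice that costs little to change. It is not evidence that selection took place.

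**What to change.** For allocations still to be made, replace the fixed blocks of four with one computer-generated list that uses randomly mixed block sizes, for example 4 and 6, or 4, 6 and 8. Do not disclose the sizes to site staff. Have the list prepared and held by someone who does not enrol, treat or assess, and use numbered envelopes opened in order.

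The gain is the near removal of certain deductions, from about 32% to about 5.5% or 2%. Best-guess accuracy falls only from 70% to 69% or 68%, because every block still returns to balance. Separating whoever holds the list from those who enrol and treat therefore matters as much as the block sizes. Including blocks of 2 would leave best-guess accuracy at about 70%.

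The cost is a short task of list preparation and a possible small final imbalance: up to three between arms with a largest block of 6, or four with a largest block of 8, against two now.

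The Study design section gives recruitment as February to June 2024. If enrolment is complete, the scheme cannot be changed. The report should then state who made, held and opened the envelopes, say whether they also enrolled or treated, and give the predictability as a limitation.
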